### Participant timeline {13}

Patients are involved in the study for wax removal. The trial requires one clinic visit for every patient. Patients will be advised to use the allocated intervention for seven days prior to their appointment and then will visit the clinic for the wax removal appointment. This is shown in the trial flow chart (see Fig. 1).

### Sample size {14}

A total sample size of 1,742 participants across 26 clusters/GP practices (67 participants in each practice) was calculated as sufficient to detect a minimal clinically important difference of 9%, with an 80% power level and 5% significance. The sample size for this trial was determined via ‘The Shiny CRT Calculator’ (accessible here: https://clusterrcts.shinyapps.io/rshinyapp/lculator: Power and Sample size for Cluster Randomised Trials (shinyapps.io)). The following parameters were used (trial design = parallel; correlation structure = exchangeable; differential clustering = false; allowance for varying cluster sizes = yes; coefficient of variation = 0.527; number of clusters per arm = 13; intracluster correlation = 0.02; ICC lower extreme = 0.01; ICC upper extreme = 0.05; outcome type = binary; proportion under control = 0.74; proportion under investigation = 0.83).

The above parameters were determined via discussion with statisticians and by professional consensus. A consensus was reached among 13 professionals regarding the minimal clinically important difference in the use of a specified pretreatment wax softener. The majority of the responses from the 13 professionals were between 6 and 10%, so for a conservative approach, we decided to use 9%, which was also the average.

The NHS Audiology wax removal service in North Wales is still in the process of roll out, and the actual number of GP practices participating in the study may be greater than 26. If this is the case, the sample size calculation will be reviewed.

### Recruitment {15}

The participants will be individual NHS patients who access the earwax removal service. They will be identified by the GP surgery administration teams or healthcare staff as per usual practice (patient contacts or is advised by healthcare professionals to request an appointment for wax removal or reporting symptoms/needs that are thought/confirmed to be because of wax build-up). The normal procedure for booking a wax removal appointment will be followed, and staff at the GP practice will be fully informed of the research. When booking the appointment, patients will be informed of the pretreatment they should use for seven days prior to their wax removal appointment by the staff member booking their appointment. Patients can book their appointment face-to-face whilst visiting the surgery or by telephone. Patients will be offered written information about using the pretreatment and will be directed to a video to watch if needed. Patients will be advised to purchase their olive oil drops or olive oil spray from a pharmacy as usual clinical care.

## Assignment of interventions: allocation

### Sequence generation {16a}

Randomisation will take place at a cluster level (GP practice) with a one-to-one allocation ratio to the two groups of olive oil drops or olive oil spray via stratified block randomisation. Stratifying was performed on the basis of site size (small, large) with block sizes of 2 and 4. A total of 26 clusters will be randomised. Randomisation is performed via the randomisation software Sealed Envelope.

### Concealment mechanism {16b}

The CI will implement the allocation sequence and inform each GP practice of their allocation via email and personal visits. All precautions will be taken to conceal the randomisation allocation from the audiology practitioners delivering the earwax removal service, but patients may accidentally disclose this, or practitioners may be able to identify the pretreatment product used on the basis of otoscopy findings. Throughout the research, each GP practice is identified and allocated by a unique numerical code only known by the CI.

### Implementation {16c}

The CI will generate the allocation sequence, enrol GP practices and assign the interventions to the clusters (GP practices). As a pragmatic trial, the research is happening within normal clinical practice; therefore, patients are not officially enrolled in the study, but rather, the GP practice staff (receptionist, healthcare staff) will inform the patient of the research when booking in for the wax removal appointment. The GP practice staff will be responsible for informing the patients of the allocated intervention (olive oil drops or spray).

## Assignment of interventions: blinding

### Who will be blinded {17a}

Care providers (audiology practitioners) and the outcome verification professional will be blinded to the assignment of interventions, but we cannot accommodate patients accidentally disclosing this information during their appointment. The majority of audiology practitioners see patients from various GP surgeries at one or more locations, meaning that they are likely to see patients who have been allocated to both the comparator and the intervention during a single clinical session. Only the CI will be aware of the complete assignment of interventions, and the primary care audiology clinical leaders and GP staff members at each individual practice will be aware of their own assigned intervention. It is not possible to blind the trial participants to the assigned intervention.

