#### Rationale

Despite earwax removal being a relatively common procedure, there is limited high-quality evidence on the most effective removal method. Many studies recommend the use of a wax softener prior to mechanical removal [18]. Wax softeners have been used for many years in all healthcare settings for the management of wax as a pretreatment prior to mechanical removal [2, 18–20]. There are various pretreatment wax softeners available, and studies have shown no difference in the use of olive oil, water or any other wax softener [1, 13, 19–21]. Using a wax softener alone may lead to complete clearance of the wax in approximately 20–22% of cases, but most often, it needs to be combined with mechanical removal [13, 19, 22, 23].

The NHS Audiology Primary Care service in North Wales offers a wax removal service located at GP practices. This is a needs-based pathway in which patients reporting symptoms consistent with excessive earwax can self-refer, or patients can be referred by professionals who confirm the presence of earwax that restricts a full view of the tympanic membrane for earwax removal. All patients are advised to use olive oil drops or spray as a pretreatment wax softener followed by attempted earwax removal via microsuction by audiology practitioners as a first-line treatment. The service evaluation data revealed that one in four patients required a return visit for a second attempt at wax removal, with the first attempt being unsuccessful due to incomplete removal of wax, as reported by the audiology practitioner. Anecdotal evidence from our practitioners suggests that administering olive oil as a spray may lead to an improved success of wax removal compared with the traditional method of administering drops. This may be due to more effective coverage and contact with the wax, which is in agreement with Oron et al. [24], who reported that spray may penetrate deeper into the ear canal during application.

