## Methods: participants, interventions and outcomes

### Study setting {9}

The study will run within 26 NHS-funded GP practices that deliver the NHS Audiology Primary Care wax removal service across North Wales. The earwax removal service is delivered by audiology practitioners. Patients with symptoms, or a clinical need, can self-refer, be referred by their audiology practitioner, GP or other healthcare professional working in the practice. The research will not change service provision or routine clinical care for research participants or other patients seen within the service during the research timeline.

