### Strategies to improve adherence to interventions {11c}

Patient information leaflets are available at participating GP practices that specifically instruct patients to administer pretreatment olive oil as per the allocation of the GP practice. The patient information leaflet highlights that the research is being carried out to investigate any differences between these two administration methods, hence the importance of adhering to the intervention.

Staff reminder slips will be issued to GP practices to be placed in reception and administration offices. Additionally, staff members will be reminded regularly of the importance of encouraging patients to use the allocated solution both by the research team and the Audiology Primary Care team.

Following PPI feedback regarding the occasional lack of stock of olive oil spray in community pharmacies, local community pharmacy networks have been informed of the research to encourage local pharmacies to keep stock of both drops and sprays for patients to purchase locally.

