### Data management {19}

All research data will be recorded and held on a password-protected Excel spreadsheet on the internal NHS Audiology services’ online SharePoint site, as is the current practice for service evaluation. The data will be accessible by all audiology practitioners working at the wax removal service, their service leads and the CI of the trial. There will be a focus on ensuring that the data are accurate, eligible, complete, consistent and available when needed, hence the reason for it being kept in an easily accessible location. The CI will extract the required data from the source file for analysis purposes. The data will not be shared with anyone outside the research team at any time.

A numerical identification code will be allocated to the selection of patients who consent to a video otoscopy image of their ear following microsuction. This code will be added to their corresponding data input on the main spreadsheet by the CI and on their photographic consent form. The numerical code and corresponding consent form with the patient’s name will only be available and known by the CI.

Patients will have the opportunity to share their email address to receive a summary of the trial outcomes. Their email address will not be able to be linked back to their research data entry and will be shared only with the CI. The email address will be recorded on individual GP practice patient slips alongside a GP clinic code related to the research allocation. The GP clinic codes and allocated treatment details will be stored electronically on the internal NHS Audiology online Sharepoint site in a password-protected Excel spreadsheet accessible only by the CI. This will be deleted at the end of data collection.

Both the written video otoscopy consent forms and the GP practice patient slips with completed email addresses will be stored in the research file within a locked cabinet that will be accessible only by the CI.

In compliance with good clinical practice (GCP), all documentation relevant to the trial will be retained for a period of 5 years following the end of the RCT. Further information on data management can be found within the protocol.

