The research is run within 26 sites across North Wales. While the CI will maintain close contact with all the sites during the research, the risk remains that primary care staff booking the wax removal appointment and advising patients on the use of pretreatment wax softeners may not give the correct advice or may not emphasize the importance of adhering to recommended guidance. To help support this, each cluster site has been issued staff reminder slips that are displayed behind reception and in staff areas as reminders of the advice that should be given to patients.

PPI representatives were included in the development of the study design through focus groups and email correspondence. Their input shaped the design of the protocol and methodology by validating the design and informing protocol details such as the difference between olive oil sold in pharmacies for wax removal purposes and ordinary kitchen olive oil and acceptance of price differences to patients between the investigator and comparator product. All PPI individuals approved the trial as important research and supported the ethical approval process. The PPI individuals will be kept informed of the progress of the trial as the research progresses.

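### The practitioners who rate the primary outcome are described as blinded, but the plan's own procedures leave avoidable routes by which they can learn a practice's arm

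*Protocol article*

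**What the plan says.** All references are to the protocol article.

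**On blinding.** Section {17a} says: "Care providers (audiology practitioners) and the outcome verification professional will be blinded to the assignment of interventions". The same sentence excepts accidental disclosure by patients. Section {16b} promises every precaution and concedes that "patients may accidentally disclose this, or practitioners may be able to identify the pretreatment product used on the basis of otoscopy findings". Section {17a} adds that most practitioners see patients from several surgeries and are likely to meet both arms in one session. It also says that the audiology clinical leads know the allocation.

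**On where the service runs and what is kept there.** Section {9}: "The study will run within 26 NHS-funded GP practices that deliver the NHS Audiology Primary Care wax removal service across North Wales". On leaflets, {11c} says: "Patient information leaflets are available at participating GP practices that specifically instruct patients to administer pretreatment olive oil as per the allocation of the GP" (the quote stops one word before the end of the sentence). On reminder slips, the Discussion says: "each cluster site has been issued staff reminder slips that are displayed behind reception and in staff areas". Section {11c} itself places the slips in reception and administration offices.

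**On who gives reminders.** Section {11c} describes repeated reminders to staff, whose subject and source it gives as follows: "encouraging patients to use the allocated solution both by the research team and the Audiology Primary Care team".

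**On the appointment.** Section {18b} says that when a patient reports having used no softener, the practitioner still goes on to attempt removal. Section {8} has a feedback slip on the softener used given out at the end of the appointment.

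**On the rating.** Under Outcomes {12}, the practitioner's inspection defines the primary outcome: 0 or 1 in Table 1 is success, 2 or 3 is failure. Sections {8}, {26a} and {21b} describe an independent rating of images from a selection of consenting patients, used to check agreement.

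**The concern.** The primary outcome rests on a visual judgement, and the boundary that matters lies between a minor and a moderate amount of residual wax. The person who makes that judgement has also just done the procedure. Knowledge of the arm could therefore act through the rating and through the effort spent on the ear. Randomisation does not protect against either.

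The documents also suggest a direction. The Rationale says: "Anecdotal evidence from our practitioners suggests that administering olive oil as a spray may lead to an improved success of wax removal". If some raters share that expectation, bias would favour the trial's hypothesis.

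Cluster allocation makes a leak more than a single event. Once a practitioner learns one practice's product, that knowledge can apply to later patients of the practice. If {17a} stands as worded, the trial report may claim more assessor blinding than the procedures secure.

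**Working it through.** **Step 1. Set the routes against the blinding statement.**

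| Route | Source | Conceded in {16b} or {17a}? | What it supports |
|---|---|---|---|
| Patient discloses by accident | {16b}, {17a} | Yes | Practitioner can learn the arm |
| Appearance at otoscopy | {16b} | Yes | Practitioner can infer the product |
| Slips in staff areas | Discussion, {9} | No | Exposure is possible; inferred from where practitioners work |
| Arm-specific leaflets in the practice | {11c}, {9} | No | As above |
| Audiology Primary Care team reminds staff about the allocated solution | {11c} | No | Brings the delivering service into contact with allocation |
| Softener use comes up before removal is finished | {18b} | Only as accident | An opening for disclosure before the rating |
| Feedback slip at end of visit | {8} | No | At most informs ratings of later patients |

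The middle four rows are the point. They are arrangements that the plan could make differently.

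**Step 2. Ask whether the image check covers the gap.** Reading {26a} as five patients for each of 90% of practitioners gives 5 x 0.9 = 4.5 images per practitioner in the service. The number of practitioners is not stated. To cover even a tenth of the planned sample (0.10 x 1,742 = 174) would take 174 / 4.5, or about 39 practitioners. The check measures agreement and does not replace the practitioner's rating. An image taken afterwards cannot show differences in effort.

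**Step 3. Reproduce the plan's sample size ({14}).** Inputs: 0.74 and 0.83; 13 clusters of 67 per arm; ICC 0.02; coefficient of variation 0.527; 80% power; 5% significance, taken as two-sided.

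- n per arm, unclustered = (0.74 x 0.26 + 0.83 x 0.17) x (1.960 + 0.842)^2 / 0.09^2 = 323.2
- Design effect = 1 + ((1 + 0.527^2) x 67 - 1) x 0.02 = 2.692
- Total = 2 x 323.2 x 2.692 = 1,740, against 1,742 stated

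The planned size reproduces, and this point does not affect it.

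**Step 4. Illustrate the bias.** Suppose there is no true difference and both arms have 74% success. Let f be the fraction of all spray-arm failures recorded as success because the rater knows the arm. Then:

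- Bias = 0.26 x f
- Effective n per arm = 13 x 67 / 2.692 = 323.5
- SE = sqrt[(0.74 x 0.26 + p(1 - p)) / 323.5], with p = 0.74 + 0.26f

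For f = 0.10: p = 0.766, bias = 0.026, SE = 0.0339, ratio 0.767. The chance of a significant result is about 12%, against a nominal 5%.

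| f (assumed) | Bias, points | Chance of a significant result |
|---|---|---|
| 0 | 0 | 5% |
| 5% | 1.3 | 6.7% |
| 10% | 2.6 | 12% |
| 20% | 5.2 | 35% |
| 34.6% | 9.0 | 80% |

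These use the normal approximation without the plan's small-cluster correction. The fraction f is the share of spray-arm failures rated by someone who knows the arm, times the share of those that are shifted. For example, 50% x 20% = 10%. It applies to all failures, including fully occluded ears (rating 3), which are unlikely to be re-rated. The split between ratings 2 and 3 is not given.

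**The case against.** The strongest reply is that the protocol is already candid. The sentence in {17a} goes on to except disclosure by patients, and {16b} adds otoscopic clues, so a careful reader would not expect complete blinding. Because most practitioners see patients from several surgeries, a slip on the wall does not necessarily identify the arm of the patient in the chair. No section puts slips in clinic rooms, and {11c} names only reception and administration offices. An independent blinded rater also checks a sample. All of this stands, and it limits the conclusion to possible exposure. It does not account for the routes that the blinding sections leave out.

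A reader might infer more from three places, and the documents do not support it.

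- **The clinic code.** The patient slip carries an email address "alongside a GP clinic code related to the research allocation". Section {19} says the file linking codes to treatments is accessible only to the CI, so the code does not reveal the arm.
- **The reminder role.** Staff can be urged to follow the allocated solution without the reminder naming it. The clinical leads, whom {17a} already lists as aware, may be the ones who give it. The role need not mean that practitioners know the allocation.
- **The prior belief.** The Rationale reports anecdote and says spray may help. It does not show that the practitioners who rate outcomes hold that view.

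The feedback slip comes at the end of the visit, so it probably cannot influence that patient's own rating.

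**Conclusion.** The concern holds in a limited form. Sections {16b} and {17a} promise blinding and full precautions, while {11c}, {18b} and the Discussion set up avoidable ways for a practitioner to learn a practice's arm. These passages must be reconciled, because the same person operates and then gives the rating that defines the primary outcome, and the image check is too limited to stand in for it.

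It would go too far to say that practitioners do know the arm or that the materials show it to them. That practitioners see the slips is an inference from where they work.

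The size cannot be derived from the documents. At an assumed shift of 10% of all spray-arm failures, the spurious difference is 2.6 points and the false-positive rate about 12%. A shift large enough to produce the whole 9-point target (34.6% of failures) has no support in the documents and is shown only to mark the scale.

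**What to change.** 1. Keep allocation-specific slips at the booking desk and out of areas that practitioners use.
2. Have only the CI or research team give allocation reminders, not the Audiology Primary Care team.
3. Require the visualisation rating to be entered before softener use is discussed, and have reception issue and collect the softener slip. Patients may still volunteer the information.
4. Add one field, completed after the rating, for whether the practitioner knew or guessed the softener. Report it by arm as description only. Perceived allocation arises after randomisation and can depend on the arm and on residual oil, so splitting the primary result by it is not a valid subgroup test.
5. Reword {17a} to say that practitioners are intended to be blinded but that this is not assured, and name the routes above.

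**Cost.** Reminders become slightly less visible, and there is one extra data field. Section {18a}, which says nothing beyond routine data is collected, must be amended, and the changes need the approvals in {25}. No extra visits are needed. Trial status gives recruitment from January 2025, a protocol version dated August 2025 and an expected end of data collection in December 2025. Items 1 to 4 therefore affect only data collected after they are made, and the report should give the date of the change. Item 5 is worth making whatever stage the trial has reached.

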### Procedure for unblinding if needed {17b}

There is no requirement for a procedure for unblinding during this trial, as there is no risk associated with the blinding, as both interventions are the same solution only delivered in a different manner.

## Data collection and management

### Plans for assessment and collection of outcomes {18a}

The trial will use routine clinical data collected from patients accessing the audiology wax removal service. No additional data are collected as part of this research, which is not routinely collected for service evaluation. No patient identifiable data are collected, and all data are recorded at the microsuction appointment visit. The premicrosuction data recorded included date, location, age, referral source and self-reported presenting symptoms. The postmicrosuction data recorded included the amount of residual wax in each ear (visualisation rating) and the degree of improvement in self-reported presenting symptoms using a 5-point scale (much better, somewhat better, no change, somewhat worse, much worse). All the data are recorded during a single clinic visit.

All the data collected will be recorded on a password-protected Excel spreadsheet currently used by audiology practitioners for evaluation purposes. The spreadsheet is kept online on the Audiology SharePoint intranet site, meaning that it is accessible to all audiology practitioners working at various NHS locations.

Only patients with a complete outcome dataset were included in the final analysis.

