### Trial design {8}

This RCT is a parallel, two-arm, superiority cluster randomisation trial design to compare the effectiveness of olive oil drops and olive oil spray when used as a pretreatment wax softener prior to wax removal by microsuction. A cluster randomised design was chosen to ease the organisation of the trial, as it takes place within a current clinical service, and individual randomisation would add to the workload and make the trial difficult to undertake. Twenty-six GP practices will be included and randomised via a one-to-one allocation ratio to either the intervention arm (olive oil spray) or the comparator arm (olive oil drops) prior to the start of the study. The trial is designed to have a pragmatic approach, with the data analysed via an intention-to-treat analysis. Figure 1 presents the trial flow chart. Minimal changes are introduced to the service as part of this trial but include:Verification of one of the secondary outcomes, which involves reporting the amount of residual wax following microsuction by the audiology practitioner. The amount of residual wax following microsuction is recorded by the audiology practitioner via a visual verification rating (0–3); see Table 1. A video otoscopy image will be taken with patient consent and sent to an independent professional, who will rate the amount of residual wax using the verification ratings. The ratings of the audiology practitioner and independent professional will be compared to verify the reliability of this outcome.Patients will be given a feedback slip at the end of the appointment with the audiology practitioner and asked to select which pretreatment wax softener they used. This information will be used to check adherence to the protocol when analysing the outcomes given that the pretreatment wax softener is purchased and self-administered by the patient.

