### Outcomes {12}

#### Primary outcome

The primary outcome is a comparison of the success of wax removal across the two groups. Success of wax removal is measured by the Audiology Practitioner, who inspects the ear and calculates the proportion of patients where wax removal is successful (0 or 1 as defined in Table 1) at the first attempt and who do not need a repeat visit (2 or 3 as defined in Table 1).

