#### Secondary outcomes

The secondary outcomes include the following:Improvements in self-reported presenting symptoms (reported by patients during clinic visits prior to microsuction) measured via a 5-point improvement rating scale (much better, slightly better, about the same, slightly worse, and much worse) following wax removal in the two groups.Differences in the amount of residual wax following microsuction are measured by a postmicrosuction visualisation rating reported by the audiology practitioner through visual inspection of the ear. See Table 1.Adverse events. All adverse events that occur in the clinic during or immediately after microsuction and any reported by patients up to one week after microsuction, will be recorded as per normal clinical practice.

A further exploratory analysis will be completed on the following:The effect of age on the success of wax removal.Success of wax removal in patients who do not use any pretreatment.

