### Methods in analysis to handle protocol nonadherence and any statistical methods to handle missing data {20c}

A sensitivity analysis will be run by removing the patients who did not use pretreatment and rerunning the analyses of the primary and secondary outcomes. As all the data are nonidentifiable, there will be no way of identifying individual patients who have not adhered to the protocol. Only patients with a full dataset were included in the analysis.

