## Discussion

This research aims to answer an important question, as deemed by PPI individuals, that has the potential to impact national guidance on wax removal procedures. This pragmatic RCT runs within a current clinical service and has been designed to reflect real-life clinical practice and minimise disruption to clinical services. Audiology practitioners at any level do not currently have prescribing rights; thus, this trial is restricted by an inability to supply the olive oil solution to patients, meaning that we have adhered to the current clinical procedure in that patients source the olive oil solution themselves. This does carry a potential risk of patients not adhering to the protocol owing to product availability, issues sourcing the solution locally or failure to follow clinical recommendations. Following PPI feedback, we have attempted to minimise this by contacting community pharmacy teams across North Wales, informing them of the research and advising them to stock both olive oil drops and olive oil spray in their pharmacies for the benefit of this research and by using patient information materials and posters that highlight the importance of this research.

The data will be analysed via an intention-to-treat analysis. This may mean that any difference between the two groups will be minimised, indicating that the pragmatic approach taken with the aim of better reflecting a real-life clinical situation may be seen as a strength of the trial. An alternative approach would need to be highly regulated, and any findings may not necessarily be effective in real life.

Data collection is to be completed by audiology practitioners, and no additional data are being collected compared with those already being collected for data evaluation purposes. We hope this will help ensure that there are no missing data entries. All audiology practitioners involved in the service will be aware of the RCT, and its objectives and clinical leaders of the service will be involved and approved for the study design.

The findings of this research will only be applicable to the use of pretreatment with the wax softener olive oil followed by the mechanical removal method of microsuction. Further research will be needed to determine whether the same findings apply to other pretreatment wax softeners or mechanical removal methods, such as irrigation.

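### As written, the completeness rule drops a patient with a valid primary rating from the primary analysis when a secondary field is missing, contrary to the stated intention-to-treat analysis

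*Protocol article*

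**What the plan says.** All references are to the protocol article.

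- **The rule, first statement.** Plans for assessment and collection of outcomes {18a}: "Only patients with a complete outcome dataset were included in the final analysis".
- **The rule, second statement.** The section on nonadherence and missing data {20c}: "Only patients with a full dataset were included in the analysis".
- **What is recorded after microsuction.** {18a} lists "the amount of residual wax in each ear (visualisation rating) and the degree of improvement in self-reported presenting symptoms using a 5-point scale".
- **What the primary outcome needs.** Under Outcomes {12} it is "the proportion of patients where wax removal is successful (0 or 1 as defined in Table 1) at the first attempt". It uses the visualisation rating and no symptom score.
- **Where the symptom score belongs.** It is a secondary outcome, "measured via a 5-point improvement rating scale".
- **The stated principle.** Trial design {8} has the trial run pragmatically, "with the data analysed via an intention-to-treat analysis". The Abstract and the Discussion say the same ("The data will be analysed via an intention-to-treat analysis").
- **Expectation on missing data.** The Discussion notes that only routine fields are collected and adds: "We hope this will help ensure that there are no missing data entries".

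**The concern.** The rule is written for the patient's whole record, not for the outcome under analysis. Taken at its word, it lets a gap in a secondary field decide who enters the primary comparison. A patient seen at a randomised practice whose first-attempt result is known would be left out because nobody recorded how the symptoms had changed. That is hard to square with intention-to-treat, under which a patient with an observed primary outcome is analysed in the allocated arm.

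Three things are at stake:

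- Usable primary data are discarded, and the sample size makes no allowance for exclusions.
- If incomplete records are more common among failures, the observed success proportions are too high.
- The article states two rules for the primary population that do not agree. Unless one is withdrawn, the choice could be made after the data are seen.

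**Working it through.** **1. Reading the rule against the outcomes.** {18a} names two outcome fields recorded after the procedure: the visualisation rating and the symptom-improvement score. Outcomes {12} also lists adverse events, including those reported up to a week later. The primary outcome is a dichotomy of the rating alone (0 or 1 against 2 or 3). A record with a rating but no symptom score is complete for the primary outcome and incomplete as an outcome dataset. No sentence in the article says that completeness is judged outcome by outcome, and the phrase used in {20c} is wider still.

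**2. Reproducing the planned sample size.** Inputs from Sample size {14}: 0.74 against 0.83, 13 clusters per arm, mean size m = 67, coefficient of variation 0.527, intracluster correlation 0.02, 5% significance (taken as two-sided), 80% power.

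- Required effective n per arm = (1.96 + 0.8416)² × (0.74×0.26 + 0.83×0.17) / 0.09² = 323.2.
- Design effect = 1 + [(1 + 0.527²) × 67 − 1] × 0.02 = 2.692.
- Effective n per arm = 13 × 67 / 2.692 = 323.5, giving power of 80.0%.

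The stated 1,742 (26 × 67) is reproduced, with nothing in hand for exclusions.

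**3. Power if records are excluded.** The share excluded is assumed, is spread evenly over practices and leaves the coefficient of variation unchanged.

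| Share excluded | Mean cluster size | Power |
|---|---|---|
| 0% | 67 | 80.0% |
| 5% | 63.65 | 79.3% |
| 10% | 60.3 | 78.5% |
| 20% | 53.6 | 76.5% |

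For the 10% row: design effect 2.52, effective n = 13 × 60.3 / 2.52 = 311 per arm. The loss is small because clustering dominates the variance.

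**4. Bias if incompleteness depends on success.** Let p be the true success proportion, and let ms and mf be the shares of successes and failures with an incomplete record. Then

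observed proportion = p(1 − ms) / [p(1 − ms) + (1 − p)(1 − mf)].

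- If ms = mf, the factor cancels, the observed proportion equals p, and the bias is zero.
- Assume ms = 5% and mf = 20% in both arms. Drops: 0.703 / (0.703 + 0.208) = 77.2%. Spray: 0.7885 / (0.7885 + 0.136) = 85.3%. The difference is 8.1 points instead of 9.0.
- In that scenario 1 − 0.911 = 8.9% of the drops arm and 1 − 0.9245 = 7.6% of the spray arm are excluded.

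**5. The same scenario on the odds scale.** Observed odds = p/(1 − p) × (1 − ms)/(1 − mf). With the same rates in both arms the last factor is common and cancels from the odds ratio: 2.846 to 4.882 without exclusions, 3.380 to 5.798 with them, a ratio of 1.715 each time. Incompleteness that is alike in both arms therefore shifts the proportions and the difference in points, but not the odds ratio from the planned logistic model.

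**The case against.** The best case for the plan is that the phrases are undefined and may only mean completeness for each outcome in turn. Statistical methods {20a} gives each outcome its own model, with the patient as unit for symptoms and the ear for residual wax. All data come from one visit, in fields that the service already collects, so gaps may be few. Intention-to-treat chiefly concerns analysis by allocation, and any workable primary set still needs an observed rating. The full protocol may also say more. What stands is that the amount of missing data may be small and an outcome-by-outcome reading is possible. What does not stand is that the article supports that reading: it states the unrestricted rule twice, once under missing data, so the matter has not simply been left to another document.

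A reader might also infer stronger claims, which the documents do not support:

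- **Abandoned procedures drop out as unrated failures.** The article describes no such patients, and Table 1 has ratings 2 and 3 for an ear that is not cleared, so a stopped attempt can be rated.
- **Patients treated for a need have no score, which ties missingness to the primary outcome.** {20a} describes the improvement outcome as covering needs as well as symptoms. Even if some of these patients lacked a score, need is fixed before microsuction, and nothing in the article links it to success or to arm.
- **The rule creates a false difference between arms.** If failure records were incomplete at 10% in one arm and 20% or 30% in the other, with 5% of successes incomplete in both and no true effect, the formula gives spurious differences of 2.1 or 4.4 points. Those rates are invented. The recording practitioners are meant to be blinded and most are likely to see patients from both arms. Blinding may leak, as the article admits, but that alone is little reason to expect incompleteness to differ by arm.

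**Conclusion.** The concern holds as a fault in the stated analysis set, of moderate severity. The rule as worded removes patients whose primary outcome is known because a secondary field is blank, and it conflicts with the announced intention-to-treat analysis. This conclusion rests on the text alone and needs no assumption about missingness.

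The consequences are a risk of unknown size, since every rate used above is assumed. Bias is zero if incompleteness is unrelated to success. With 5% of successes and 20% of failures incomplete in both arms, the difference moves from 9.0 to about 8.1 points and the odds ratio does not move. Power falls by 1.5 points at 10% exclusion and 3.5 points at 20%. The documents do not show that the primary comparison will be biased, or that either arm would be favoured.

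**What to change.** Replace the sentences in {18a} and {20c}, and align the full protocol and any analysis plan, so that:

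- the primary analysis includes every eligible patient with a first-attempt visualisation rating, in the arm to which the practice was allocated, regardless of any other field;
- each secondary outcome is analysed in all patients who have that outcome;
- the number and share with each outcome missing are reported by arm;
- if primary ratings are missing, a simple best-/worst-case analysis by arm accompanies the primary result. The absence of this analysis from a condensed article is not itself a fault.

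Under this rule a missing symptom score costs the primary analysis nothing, and power stays at the planned 80.0% with 1,742 rated patients. The cost is the change of wording, denominators that differ between outcomes and must be shown in the tables, and at most one extra analysis. No added patients or data fields are needed. The change should be made and dated before outcomes are compared by arm.
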